### 4.3. Standard Operating Procedures

#### 4.3.1. Completing the Clinical Questionnaire

(1) To be familiar with the operating procedures, the investigators are expected to read the entire content of the eCRF, instructions on program implementation, and the investigator's handbook carefully before starting the clinical study. (2) Each investigator will have his own separate eCRF account (website: www.medresman.org) to timely, accurately, and thoroughly record each item according to a unified recording method. (3) After recording is complete, each investigator should double-check the information to ensure that there are no omissions or misinformation. (4) If any content in the questionnaire needs to be modified, investigators should indicate the reason for the revision. In addition, any modification process will be recorded by eCRF.

#### 4.3.2. Collecting TCM Symptoms

(1) In the process of collecting clinical information, the investigator should listen patiently and record information carefully. In addition, language should be easily understood by patients, and the use of complicated terminology should be avoided. (2) Each symptom will be divided into four degrees, including “no”, “light”, “medium”, and “heavy”. The instruction of how to classify the degree of each symptom is included in the investigator's handbook. (3) When observing the body and tongue, the investigator should fully expose the parts of the body and examine them under nature light, avoiding the use of colored light. Each tongue should be observed for no more than 30 seconds. If the primary observation of the tongue is not confirmed, patients should rest for 3-5 minutes and investigator may repeat the observation. At this point, for the tongue diagnosis, investigators may refer to the color map in their handbook. (4) Pulse diagnosis is conducted with the radial artery by an experienced TCM practitioner.

#### 4.3.3. Collecting CAG Result and GRACE Score

The CAG result will be judged by the imaging physician. The unified quality control method will be employed to guarantee the accuracy of the GRACE score of each participant, according to international grading standards [12].

#### 4.3.4. Information Management

(1) Patient code: every site has a 2-digit code (Table 1). According to the patient's enrollment order, the corresponding code will be produced. For instance, when Guang'anmen Hospital recruits the first patient, the code will be 01-0001. (2) Dynamic management: by using eCRF, the registration information of the patient will be uploaded synchronously, which will make it simple for the PI to check it in real time. (3) Data collection: to ensure the objectivity and accuracy of the collected data, we recommend that at least two investigators oversee data collection. The diagnosis of the tongue and pulse must be performed by at least two experienced TCM practitioners, and the CAG results should be interpreted by at least two experienced imaging physicians. If there is any disagreement, it will be resolved by discussion and be arbitrated by a third physician. (4) Data entry: all data must be completed by the investigators using the eCRF procedure within 24 of enrollment to ensure accuracy of the data. (5) Data submission: before submitting the eCRF, it should be approved by the PI in charge of the specific site.

### 4.4. Supervision and Internal Inspection

(1) The monitor will randomly conduct on-site or telephone supervision of the sites and ensure that the study is strictly following the protocol. (2) Content for supervision includes informed consent, standardized collection of clinical information, and accuracy of the raw data. (3) The PI of each site should regularly conduct internal inspections to find and resolve problems in timely manner.

## 5. Statistical Analysis

All data will be exported in an Excel-format through the www.medresman.org. The methods for statistical analysis include frequency analysis, factor analysis, cluster analysis, decision tree, and other relevant analytic methods. SPSS 20.0 will be used for statistical analysis.

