**Methods and Design:**

This is a multicenter, large sample, case series study in 4 tertiary A hospitals from 3 provinces in China. A total of 3,000 eligible patients diagnosed with atherosclerosis or CHD and selected to undergo coronary angiography (CAG) will be enrolled in this study. We will use electronic case report forms (eCRF) to collect information, including baseline characteristics, TCM symptoms, CAG results, and GRACE scores according to standard operating procedures (SOP). Data will be analyzed by SPSS 20.0.

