## 2. Objective

The study aims to determine the association between TCM Zheng and types of coronary artery stenosis and to determine the association between TCM Zheng and GRACE score.

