## 3. Methods and Design

### 3.1. Study Design

This study is a multicenter, large sample, case series study. The Declaration of Helsinki and Good Clinical Practice (GCP) Guidelines are regarded as the principle of this clinical study. The protocol, informed consent, and electronic case report form (eCRF) of this study have been reviewed and approved by the Ethics Committee of Guang'anmen Hospital of the China Academy of Chinese Medical Sciences (no. 2017-058-KY-01). The participants' information and privacy will be strictly protected. Written informed consent will be obtained from each participant before the clinical information is collected. This study was registered at the Chinese Clinical Trial Registry on November 2, 2017, in both Chinese and English editions; the registration number was ChiCTR-ROC-17013221. The study design is briefly described in Figure 1.

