### 3.3. Diagnostic Criteria

#### 3.3.1. Traditional Chinese Medicine Diagnostic Criteria of CHD Zheng

TCM Zheng of each participant will be estimated by two TCM experts referring to the “National Standard Clinical Terminology of Traditional Chinese Medical Diagnosis and Treatment–Syndromes (GB/T 16751.2-1997)” and “Traditional Chinese Medicine Syndrome Differentiation Criteria of Coronary Heart Disease” [6]. These two diagnostic criteria involve all the simple Zheng. Permutations and combinations of these simple Zheng are flexible and could encompass all the complex clinical settings. The interrater reliability of diagnosing TCM Zheng will be evaluated using the kappa statistic.

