**Figure 2 fig2:**
[figure not shown]
The possible association between TCM Zheng and coronary artery stenosis.

**Table 1 tab1:** The hospitals participating in this study.

Code	Participating Center	Code	Participating Center
01	Guang'anmen Hospital, China Academy of Chinese Medical Sciences	03	Yunnan Provincial Hospital of Traditional Chinese Medicine
02	Beijing Anzhen Hospital Capital Medical University	04	The First Affiliated Hospital of Xinxiang Medical University

**Table 2 tab2:** Indications for revascularization in patients with stable coronary artery disease.

Extent of CHD	Class	Level
For prognosis		
Left main disease with stenosis >50%	I	A
Any proximal LAD stenosis >50%	I	A
Two-vessel or three-vessel disease with stenosis >50% with impaired LV function (LVEF<40%)	I	A
Large area of ischaemia (>10% LV)	I	A
Single remaining patent coronary artery with stenosis >50%	I	B
For symptoms	I	C
Any coronary stenosis >50% in the presence of limiting angina or angina equivalent, unresponsive to medical therapy	I	A

LAD: left anterior descending coronary artery; LV: left ventricular.

**Table 3 tab3:** Recommendation for type of revascularization (CABG or PCI) in patients with stable coronary artery disease.

Extent of CHD	CABG		PCI	
	Class	Level	Class	Level
One- or two-vessel disease without proximal LAD stenosis	IIb	C	I	C
One-vessel disease with proximal LAD stenosis	I	A	I	A
Two-vessel disease with proximal LAD stenosis	I	B	I	C
Left main disease with a SYNTAX score 22	I	B	I	B
Left main disease with a SYNTAX score 23-32	I	B	IIa	B
Left main disease with a SYNTAX score >32	I	B	III	B
Three-vessel disease with a SYNTAX score 22	I	A	I	B
Three-vessel disease with a SYNTAX score 23-32	I	A	III	B
Three-vessel disease with a SYNTAX score >32	I	A	III	B

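### The objective is to determine associations of Zheng with stenosis type and with GRACE score, but none of the named analyses gives an adjusted association estimate with a confidence interval

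*Protocol article*

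**What the plan says.** Section 2 (Objective) of the protocol article reads: "The study aims to determine the association between TCM Zheng and types of coronary artery stenosis". The same sentence sets a second aim of the same kind for GRACE score. Section 3.1 describes the design: "This study is a multicenter, large sample, case series study". The abstract adds that there are four hospitals, all tertiary A, in three provinces.

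Section 5 (Statistical Analysis) is three sentences long: how data are exported, which methods are used, and the software (SPSS 20.0). The sentence on methods is: "The methods for statistical analysis include frequency analysis, factor analysis, cluster analysis, decision tree, and other relevant analytic methods". The section names no model with stenosis type or GRACE score as the outcome and Zheng as the exposure.

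Three other places bear on this:
- Section 3.5 (Sample Size) appeals to multifactor analysis with about 100 variables to justify 3,000 patients, but names no multivariable model.
- Section 3.6 lists the data collected, including age, sex, height, weight, smoking and alcohol history, past medical history and medication, as well as Zheng, the angiography result and GRACE score.
- Section 4.3.4 puts a hospital code in every patient number.

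**The concern.** The stated question and the stated methods do not meet. A reader of the results will want to know how much more often a given Zheng occurs in one stenosis type than in another, how GRACE score differs with and without it, how precisely that is known, and whether it survives allowance for obvious common causes. The named methods leave most of this unanswered.

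The stakes are those of any unrandomised comparison. If hospitals differ both in how often a Zheng is recorded and in which stenosis types they see, a crude table shows an association even when none exists inside any hospital. Age, sex, smoking or other illness could do the same. The Discussion (section 6) hopes that Zheng may help identify risk factors for progression of stenosis, and crude percentages would be weak support for that.

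**Working it through.** **Step 1. Each named method against the objective.**

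| Method | Outcome? | Adjusted effect with interval? |
|---|---|---|
| Frequency analysis | Can cross-tabulate Zheng by stenosis type | No; crude |
| Factor analysis | None; groups variables | No |
| Cluster analysis | None; groups patients or variables | No |
| Decision tree | Can take stenosis type or GRACE as target | No; gives splits and predictions |

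The remaining item in the list is an open clause and commits to no method.

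**Step 2. The sample size used below.** Section 3.5 gives 100 × 25 × (1 + 15%) = 2,875, which the article rounds up to about 3,000. Dividing by 0.85 instead gives 2,500 / 0.85 = 2,941, also near 3,000. The article's N = 3,000 is used here.

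**Step 3. How large could confounding by hospital be?** The article gives no rates by hospital, so every rate below is an assumption, as is the choice of which hospital gets which rate. The setting has one Zheng (present or absent), one binary stenosis outcome (severe or not), four equal hospitals, and Zheng and stenosis independent inside each hospital. With z and s the Zheng and stenosis rates in a hospital, the pooled cells are averages over hospitals:

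a = mean of z·s; b = mean of z(1−s); c = mean of (1−z)s; d = mean of (1−z)(1−s); pooled OR = ad / (bc).

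For example, take Zheng 50/35/50/40% and stenosis 20/45/20/35%:
- a = (0.1000 + 0.1575 + 0.1000 + 0.1400)/4 = 0.1244
- b = (0.4000 + 0.1925 + 0.4000 + 0.2600)/4 = 0.3131
- c = (0.1000 + 0.2925 + 0.1000 + 0.2100)/4 = 0.1756
- d = (0.4000 + 0.3575 + 0.4000 + 0.3900)/4 = 0.3869
- OR = (0.1244 × 0.3869)/(0.3131 × 0.1756) = 0.875, although the OR inside every hospital is 1.

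**Step 4. False-positive rates.** From 20,000 simulated studies per row, two-sided 0.05, comparing a crude pooled chi-square test with a hospital-stratified Mantel-Haenszel test:

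| Zheng by hospital (%) | Severe stenosis by hospital (%) | Pooled OR | Crude | Stratified |
|---|---|---|---|---|
| 40/40/40/40 | 30/30/30/30 | 1.00 | 4.9% | 4.9% |
| 45/40/45/40 | 25/35/25/35 | 0.98 | 6.0% | 4.9% |
| 45/35/45/35 | 25/35/25/35 | 0.95 | 9.5% | 5.1% |
| 50/35/50/40 | 20/45/20/35 | 0.875 | 39% | 5.1% |
| 60/30/60/40 | 15/50/15/35 | 0.69 | 99.7% | 5.0% |

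The Mantel-Haenszel OR is about 1.00 in every row. Giving the fourth row unequal hospital shares (15/50/15/20%) changes its crude rate only to 38%.

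**Step 5. Hand check of the fourth row.** Overall Zheng rate = 0.4375 and stenosis rate = 0.30. Excess in cell a = 0.124375 − 0.4375 × 0.30 = −0.006875. Expected |z| = √3,000 × 0.006875 / √(0.4375 × 0.5625 × 0.30 × 0.70) = 1.66. The chance of exceeding 1.96 is then about P(Z > 0.30) = 0.38, in line with the simulated 39%.

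**The case against.** The strongest reply is that a journal article condenses a fuller plan. Its list of methods is open-ended, and the sample-size section speaks of multifactor analysis, so some multivariable work is evidently intended. Covariate lists and the handling of hospitals commonly sit in an analysis plan. The objective does not use the word adjusted, and for a case series a cross-tabulation of Zheng by stenosis type does address association, crudely. A decision tree with hospital and patient characteristics among its candidate predictors is a genuine multivariable method.

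Much of this stands. The absence of a covariate list or a hospital term is not the point here, and the tree and the tables are not worthless. What does not stand is the idea that the open clause repairs the mismatch. The article chose to name methods, and those it named do not deliver an adjusted estimate with an interval. The open clause leaves the central model to be chosen later.

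Several stronger readings are tempting, and the documents do not support them:
- **That the four hospitals are very different.** Names in Table 1 such as "Yunnan Provincial Hospital of Traditional Chinese Medicine" and "The First Affiliated Hospital of Xinxiang Medical University" suggest different kinds of institution. But the abstract calls all four tertiary A, and no case mix or recruitment quota by hospital is given.
- **That the plan pools hospitals, ignores site or leaves covariates unused.** The article is silent on which variables enter which analysis, and silence does not establish any of these.
- **That Zheng raters differ by hospital.** Section 3.3.1 has two TCM experts per participant, shared criteria and a kappa statistic. Section 4.2 trains all investigators, and section 4.3.4 provides third-physician arbitration for tongue and pulse diagnosis.
- **That the Zheng tables must be too sparse to read.** Section 3.3.1 says "Permutations and combinations of these simple Zheng are flexible and could encompass all the complex clinical settings", but no table of every combination by stenosis type is planned, and the Zheng named in the Discussion are examples from the literature.

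**Conclusion.** The point holds as a mismatch between objective and named methods: two association aims, and no named method that estimates either association with adjustment and a confidence interval. It rests on the article's own text and needs no assumption about the hospitals.

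The consequence cannot be sized from the documents. The false-positive range of about 5% to nearly 100% shows only that harm depends on hospital differences nobody can see in the article. If those differences are small, crude and stratified results will nearly agree. The illustration covers one Zheng and a binary stenosis outcome at the full 3,000. It does not cover GRACE score, and stratifying by hospital removes confounding by hospital only, not by age, sex or other characteristics.

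It is worth correcting before the data are analysed, because the remedy is cheap and the data it needs are already planned.

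**What to change.** In section 5, name two main analyses:

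1. A multinomial logistic regression of stenosis type, with each simple Zheng as its own yes/no exposure, reporting odds ratios with 95% confidence intervals.
2. A linear regression of GRACE score on the same Zheng indicators, reporting mean differences with 95% confidence intervals.

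Both should carry a hospital term and a short, prespecified set of baseline covariates from section 3.6, such as age, sex, body mass index from height and weight, smoking, past medical history and medication. In the GRACE model, leave out any covariate that is itself a component of the score. The article does not list the components, so they should be read from the grading standard cited in section 4.3.3. Label the factor, cluster and tree analyses as exploratory.

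The cost is a change of wording, a little more analysis work and slightly wider intervals. Hospital is already in the patient code, the covariates are already collected, and SPSS 20.0 fits both models.

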## 6. Discussion

CHD is usually caused by atherosclerosis, which leads to coronary artery stenosis and myocardial ischemia. The treatment strategies for CHD include mainly drugs, PCI, and CABG. It is notable that different degree of coronary artery stenosis may bring about different clinical manifestations and outcomes. In general, patients with atherosclerosis do not have symptoms of chest pain; patients with borderline coronary lesion could manifest as stable angina; patients scheduled to undergo PCI or CABG or those unable to undergo revascularization have similar symptoms including acute coronary syndrome. Studies have indicated that some kinds of TCM Zheng, such as Qi deficiency, Yin deficiency, Yang deficiency, blood stasis, phlegm, and Qi stagnation, may be found in patients with CHD [13]. Within the framework of TCM theory, different TCM Zheng has different clinical manifestations. For instance, the CHD patient with Qi deficiency could present with chest distress, shortness of breath, lassitude, spontaneous sweating, pale tongue with white coating, and weak pulse. In addition, the CHD patient with blood stasis could manifest symptoms such as a steady stabbing pain in the chest, dark complexion, cyanotic lips and nails, scaly skin, subcutaneous ecchymosis, dark and purple tongue with ecchymosis or spots, thread, and rough or knotted and intermittent pulse. Coronary artery stenosis involves several pathophysiological aspects such as endothelial injury, lipid accumulation, intraplaque hemorrhage, platelet aggregation, and thrombogenesis, which, from the perspective of TCM Zheng, could be prevented; blood stasis and phlegm could be addressed within the framework of TCM theory [14]. Previous cross-sectional studies have often analyzed the relationship between TCM Zheng and CHD, and the inclusion criteria usually used computed tomography angiography to diagnose CHD [15]. However, in this study, we focus on CHD patients who are diagnosed by the golden standard of CAG. We are expanding the population of participants to include not only CHD patients with more than 50% coronary stenosis but also patients with simple atherosclerosis and those with 30%-50% coronary stenosis [16]. In recent years, relevant studies have found that some patients with ACS are diagnosed with normal arteries, which may result from microvascular disease and endothelial dysfunction [17]. Therefore, we hope to see if differences among varying degrees of coronary artery stenosis can be identified in TCM Zheng, which may help indicate if TCM Zheng could identify risk factors for the progression of coronary artery stenosis. The possible association between TCM Zheng and coronary artery stenosis is shown in Figure 2. Among the studies assessing TCM Zheng in CHD, we are the first to assess the GRACE score of participants, which may predict long-term cardiovascular endpoint events [18] and identify those associated with different TCM Zheng.

## Figures and Tables

**Figure 1 fig1:**
[figure not shown]
Study flow chart. CHD: coronary heart disease; TCM: traditional Chinese medicine; CAG: coronary angiography; PCI: percutaneous coronary intervention; CABG: coronary artery bypass grafting.

**Figure 2 fig2:**
[figure not shown]
The possible association between TCM Zheng and coronary artery stenosis.

**Table 1 tab1:** The hospitals participating in this study.

Code	Participating Center	Code	Participating Center
01	Guang'anmen Hospital, China Academy of Chinese Medical Sciences	03	Yunnan Provincial Hospital of Traditional Chinese Medicine
02	Beijing Anzhen Hospital Capital Medical University	04	The First Affiliated Hospital of Xinxiang Medical University

**Table 2 tab2:** Indications for revascularization in patients with stable coronary artery disease.

Extent of CHD	Class	Level
For prognosis		
Left main disease with stenosis >50%	I	A
Any proximal LAD stenosis >50%	I	A
Two-vessel or three-vessel disease with stenosis >50% with impaired LV function (LVEF<40%)	I	A
Large area of ischaemia (>10% LV)	I	A
Single remaining patent coronary artery with stenosis >50%	I	B
For symptoms	I	C
Any coronary stenosis >50% in the presence of limiting angina or angina equivalent, unresponsive to medical therapy	I	A

LAD: left anterior descending coronary artery; LV: left ventricular.

**Table 3 tab3:** Recommendation for type of revascularization (CABG or PCI) in patients with stable coronary artery disease.

Extent of CHD	CABG		PCI	
	Class	Level	Class	Level
One- or two-vessel disease without proximal LAD stenosis	IIb	C	I	C
One-vessel disease with proximal LAD stenosis	I	A	I	A
Two-vessel disease with proximal LAD stenosis	I	B	I	C
Left main disease with a SYNTAX score 22	I	B	I	B
Left main disease with a SYNTAX score 23-32	I	B	IIa	B
Left main disease with a SYNTAX score >32	I	B	III	B
Three-vessel disease with a SYNTAX score 22	I	A	I	B
Three-vessel disease with a SYNTAX score 23-32	I	A	III	B
Three-vessel disease with a SYNTAX score >32	I	A	III	B
